### Evaluation of adherence

2.16

Adherence will be measured at 4, 8 and 12 weeks via online questionnaires. For both groups, participants will provide information regarding the average number of hours per day and number of days they have worn the shoe inserts (arch contouring foot orthoses or sham inserts) and their shoes in the last 4 weeks. The average time spent wearing shoe inserts when in their shoes will then be calculated [35]. Participants will be classified as adherent if they wear their shoe inserts for an average of at least 35 h per week. To minimise participant burden, adherence will be documented on the day with recall over the previous 4 weeks rather than daily entry surveys [51, 52, 53].

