### Statistical analysis

2.20

Statistical analysis will be performed using the most recent version of SPSS available to the researchers using the intention‐to‐treat principle for all randomised participants. In participants with bilateral symptoms, the more painful side will be analysed (or the right lower limb if they cannot decide which is the more painful side) to maintain independence of data [58]. Standard tests to assess continuous data for normal distribution will be used. If continuous data is not normally distributed, transformation will be carried out if appropriate. Multiple imputation will be used to replace any missing data using five iterations, with sex, age, baseline scores and group allocation as predictors [59]. The exception will be for the GROC scale, co‐interventions, adherence and adverse events where no data substitution will be applied.

The primary outcome measure will be NRS pain measured at 12 weeks. To avoid over‐testing and to minimise the risk of type I error associated with serial measurements, statistical analysis of the efficacy of the interventions will specifically focus on the between group difference at 12 weeks [60, 61]. Differences in the primary and secondary outcome measures between the two groups will be compared. Continuously scaled outcome measures will be analysed using the analysis of covariance (ANCOVA) with baseline scores and intervention group entered as independent variables [62, 63]. Dichotomous outcome measures (e.g. frequency of adverse events, frequency of co‐interventions and dichotomised GROC) will be compared using relative risk, risk difference and number needed to treat. Intervention adherence will be compared using independent group *t*‐tests. For all analyses, both 95% confidence intervals and *p*‐values will be generated where appropriate.

A sensitivity analysis will be conducted to estimate treatment effects on the primary outcome. We will assess the robustness of the results from our analyses using the following conditions: (i) complete case analysis—only analyse participants who provide outcome data and (ii) last observation carried forward. A sensitivity analysis will also be undertaken to estimate treatment effects on the primary outcome assuming full adherence (per‐protocol analysis) [64]. Full adherence will be defined as participants reporting wearing the shoe inserts for an average of at least 35 h per week.

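### The full-adherence analysis, as most naturally read an ANCOVA among wearers of at least 35 h per week, does not in general estimate the effect under full adherence

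*Protocol article*

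**What the plan says.** The main analysis in section 2.20 is run "using the intention‐to‐treat principle for all randomised participants". Continuous outcomes are compared by "analysis of covariance (ANCOVA) with baseline scores and intervention group entered as independent variables". No other model for a continuous outcome appears in the article.

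Among the sensitivity analyses for 12-week pain, section 2.20 then adds: "A sensitivity analysis will also be undertaken to estimate treatment effects on the primary outcome assuming full adherence". It labels this per-protocol and cites a method reference. The next sentence supplies the definition: "Full adherence will be defined as participants reporting wearing the shoe inserts for an average of at least 35 h per week".

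Section 2.16 (Evaluation of adherence) applies the same cut-off to both arms: "Participants will be classified as adherent if they wear their shoe inserts for an average of at least 35 h per week". On timing and source it says: "Adherence will be measured at 4, 8 and 12 weeks via online questionnaires". Missing wear data are not imputed: "The exception will be for the GROC scale, co‐interventions, adherence and adverse events where no data substitution will be applied".

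The article names no weights, instrument or predictors of adherence for this analysis.

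**The concern.** The plan names a causal target, the effect on pain if everyone adhered, but fixes only a label and a threshold. The label, a definition that picks out a set of participants, and a single stated model together point to an ANCOVA among those who reached 35 h per week.

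That set is formed after randomisation, from self-report. The two devices differ in ways that could affect tolerance. One is a heat-moulded arch device, with a varus wedge added at higher foot posture index scores (section 2.10.1). The other is a 3 mm flat insert (section 2.10.2). If people whose foot hurts more stop wearing one device more readily than the other, the remaining wearers differ in prognosis between arms. Adjusting for baseline pain does not remove selection on later pain.

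At stake is the reading of one supportive result. It could be taken as the effect of orthoses that are actually worn, when part of it, in either direction, reflects who kept wearing them.

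**Working it through.** **The plan's own figure first.** Inputs from section 2.19: difference 1.1, SD 2.2, power 80%, alpha 0.05 (two-sided fits), loss 10%.

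n per arm = 2 x (1.960 + 0.842)^2 x 2.2^2 / 1.1^2 = 2 x 7.85 x 4 = 62.8, so 63. Then 126 / (1 - 0.10) = 140. The stated 140 is reproduced and is not in question.

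**Bias of an adherers-only ANCOVA when there is no true effect.**
- From the document: SD 2.2, and ANCOVA on baseline and group.
- Assumed, because the article gives no figures: 60% adherent in each arm, correlation of 0.4 between baseline and 12-week pain, and a logistic model in which the log-odds of reaching 35 h per week fall by b per NRS point of 12-week pain.
- Method: large-sample simulation (up to 1,000,000 per arm), keeping adherers only. The estimate is orthoses minus sham, so negative values favour orthoses. Ranges show the spread between repeat runs.

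| b, orthoses | b, sham | Estimate (truth 0) | Size relative to 1.1 |
|---|---|---|---|
| 0.3 | 0.3 | 0.00 | 0% |
| 0.3 | 0.2 | -0.13 | 12% |
| 0.3 | 0.15 | -0.20 to -0.22 | 18-20% |
| 0.2 | 0 | -0.31 | 28% |
| 0.3 | 0 | -0.44 to -0.45 | 40-41% |
| 0.5 | 0 | -0.66 to -0.67 | 60-61% |
| 0 | 0.3 | +0.44 to +0.45 | 40-41% |

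With baseline correlation 0.6 the orthoses-only values shrink to -0.24, -0.35 and -0.51, and the sham-only value to +0.34.

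**Second adherence model.** Adherence was cut from a latent variable correlated 0 to 0.5 with prognosis, with 50-80% adherent and baseline correlation 0.5. Here a positive value means benefit.
- True benefit 1.1: the adherers-only estimate ranged from 0.81 to 1.57. It was 1.09 when adherence was unrelated to prognosis and 1.10 when selection was identical in both arms.
- True benefit 0: it ranged from -0.28 to +0.48.

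**Randomisation-based alternative.** Complier-average effect = intention-to-treat difference / share of the orthoses arm reaching 35 h per week. In the second model this returned 1.10 to 1.11 (truth 1.1) and 0.00 to 0.01 (truth 0) throughout, given no effect in non-adherers.

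If that assumption fails, the estimate is inflated. Suppose the full-adherence benefit is 1.1, 60% adhere and non-adherers get a quarter of the benefit. The intention-to-treat difference is then 1.1 x (0.60 + 0.40 x 0.25) = 0.77, and 0.77 / 0.60 = 1.28.

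**Precision.** At 60% adherence, 126 evaluable participants become 126 x 0.60 = 75.6. Power for a standardised difference of 0.5 (t-test) falls from 0.80 to 0.57. The complier-average interval is about 1 / 0.60 = 1.67 times as wide as the intention-to-treat interval.

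**The case against.** **The text does not say that non-adherers are excluded.** A reader might infer that section 2.20 fixes an adherers-only comparison. It does not. The complete-case analysis in the same paragraph states its restriction in so many words, and this one does not. The stated target also fits a causal estimator in all randomised participants, the method reference is not at hand, and such detail may sit in an analysis plan. This stands, so the point is put as the most natural reading. It does not dissolve the point, because what the article does fix (a causal target, a per-protocol label and a threshold) leads a reader to the wrong estimator.

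**The comparison need not be biased.** A reader might infer that it can never estimate the target. That is too strong, since the bias is nil when selection is equal. The article offers some ground for similar selection: limited disclosure to participants (2.8), a sham of the same colour, branding and foam (2.10.2), the same wear advice (2.10.3), and a stated main barrier of having to wear usual footwear, which applies to both arms (Discussion). This makes the one-arm scenarios extremes, but it does not establish equality for devices of different shape.

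**Missing wear data.** A reader might infer that everyone with any missing wear report drops out. The article says only that adherence is not imputed. It is collected three times, and the handling of a partly missing record is not stated.

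**Consequence.** This is one of several sensitivity analyses, and the primary conclusion does not rest on it. That stands and limits the weight of the point.

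**Conclusion.** The concern holds in this form: the planned full-adherence analysis, as most naturally read, is a non-randomised contrast that does not in general estimate its stated target. It does so only if adherence is unrelated to prognosis or selection is the same in both arms, and the plan gives no sufficient ground for assuming either.

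Under the stated assumptions and no true effect, the bias is 0 with equal selection, about -0.1 to -0.2 points with moderately unequal selection, and -0.3 to -0.7 or about +0.4 with selection in one arm only, against a target of 1.1. The adherence rate, correlation and slopes are illustrative, so these figures show what is possible and do not forecast the trial. The documents do not support a claim that the trial's main result is compromised: the intention-to-treat analysis is untouched. The change is worth making, but it is not critical.

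**What to change.** In section 2.20, or in the analysis plan before unblinding:

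1. Estimate the full-adherence effect in all randomised participants with a complier-average (instrumental-variable) model: allocation as instrument, wearing the orthoses at least 35 h per week as exposure, baseline pain as covariate.
2. State the assumption that allocation has no effect below that threshold, and that partial wear that helps would inflate the estimate. Say also that the contrast is with sham inserts as worn, and that the result applies to those who would reach the threshold if given orthoses.
3. State how participants with missing wear data are handled, since their pain scores are imputed and their adherence is not.
4. Report any adherers-only comparison as a non-randomised, supportive description, not as the effect under full adherence.

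Two alternatives should not be used in place of this. Weighting adherers by baseline pain does not remove selection on later pain: in the same simulation it left -0.31, -0.45, -0.68 and +0.45. Scaling mean hours linearly to 35 h adds a dose-response assumption and treats a minimum as a dose. With mean wear of 42 h, for example, it would shrink the effect to 35 / 42 = 0.83 of the intention-to-treat difference.

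The cost is a few sentences and one more model. Allocation, wear and baseline pain are already collected. The downside is a wider confidence interval and an assumption that cannot be tested.

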## DISCUSSION

3

The aim of this randomised controlled trial is to evaluate the efficacy of arch contouring foot orthoses for midfoot OA. Our recent systematic review [22] identified no fully‐powered randomised controlled trials that had evaluated interventions for midfoot OA, so our parallel‐group superiority trial will be the first adequately powered randomised controlled trial for this condition.

Our randomised controlled trial has several strengths. Firstly, to minimise the risk of bias, we will use an external randomisation service for sequence generation and allocation concealment, and the trial methodology includes participant blinding and blinded data analysis. Secondly, we will reduce attrition by minimising the burden on participants through online data collection during follow‐up. Additionally, participants can contact the study investigators if they experience any adverse events. Thirdly, the study findings are likely to be generalisable, since the trial methods, including choice of intervention and timing of outcomes, have been informed by the findings of our recent national survey of Australian podiatrists regarding their assessment and management approaches for midfoot OA (manuscript in preparation). Further, the specific type of arch contouring foot orthoses we are using are relatively low cost and widely used in Australia (as well as other countries worldwide). Finally, the choice of outcome measures of pain, function, physical activity, health‐related quality of life and adverse events is based on expert (OMERACT: Outcome Measures in Rheumatology Initiative) guidelines [65], further enhancing the external validity of the trial findings. Therefore, outcomes from our trial will provide much‐needed generalisable evidence regarding the efficacy of a common intervention, arch contouring foot orthoses, for radiographically confirmed midfoot OA.

An important consideration of our randomised controlled trial is the diagnostic criteria that we have used for midfoot OA. There is currently no agreed‐upon diagnostic criteria for midfoot OA. Traditionally, a radiographic score of two (out of a maximum of three for osteophytes or joint space narrowing) has been considered as ‘definite OA’ [27]. However, recent guidelines from NICE suggest diagnosing OA clinically without imaging in individuals aged 45 or older who experience activity‐related joint pain [37]. Given the complexity of the midfoot, we have included both activity‐related joint pain and radiographic evidence of OA in our inclusion criteria to enhance the specificity of our diagnosis. Further, we have set the radiographic OA severity score at one, instead of two, for osteophytes or joint space narrowing to increase the sensitivity of our diagnostic criteria and to improve the generalisability of our trial findings. While we acknowledge that other sophisticated imaging techniques, such as MRI, may be more sensitive for diagnosing early stages of OA [18], they were not considered feasible in our current trial due to cost and participant burden.

One limitation of the trial is the inability to blind the research staff administering the interventions. This is recognised as a common limitation in trials using non‐pharmacologic interventions [66]. However, as the outcomes are participant‐reported and participants are blinded by limited disclosure, the study can be considered assessor‐blinded. Blinding is important to avoid overestimating effects of the intervention [67]. In addition, the most likely barrier for adherence to the intervention is the requirement of participants to wear their usual footwear. We plan to overcome this by limiting enrolment during the primary holiday period in Australia (end of December to January), where it is the height of summer.

### Trial status

3.1

This study commenced recruitment in September 2023 and the first participant completed baseline testing on 14 September 2023. We envisage that the 12‐week follow ups of all participants will be completed by December 2024. The findings will be disseminated via peer‐reviewed journal articles and presented at national and international conferences from 2025. Further, the findings will be presented in a PhD thesis by [name].

## ETHICS STATEMENT

This study has obtained approval from the La Trobe University Human Research Ethics Committee (reference number: HEC23237) and all participants will provide written informed consent.

## CONSENT FOR PUBLICATION

Not applicable.

## Data Availability

On completion and publication of the study, de‐identified data may be accessed from the corresponding author upon reasonable request.
